**Trial participation/ clinical care**										
Parent/guardian information	X									
Informed consent		X								
Cross-sectional study/ HIV testing	X									
Clinical assessment	X	X		X	X	X	X	X		
Enrolment form		X								
Mother's form		X								
Follow up form				X						
Routine care	X	X	X	X	X	X	X	X	X	X
Drug administration		X	X							
Blood culture		X								
PK sampling						X	X	X		
In depth interviews									X	
Death					X					
Discharge					X					
Serious adverse event										X

### Participant Randomization

Randomization lists will be generated by the Trial statistician, using a computer, so that the study clinical team remain blinded about the allocation of the next child to be enrolled. The study coordinator will arrange for randomization codes to be printed onto cards placed in opaque sealed envelopes, a system that has worked well in other trials in acutely sick children. The envelopes will be stored on the ward and will be numbered consecutively and opened in numerical order by the study doctor.

### Data Management and Statistical Analysis

A database will be designed to capture the patient data from the study tools. Data will be checked for completeness before entry into the database. The database will be backed up on a daily basis. The study tools for each patient will be put in separate folders and kept in lockable cabinets. The primary outcome will be in hospital mortality. Secondary outcomes will be: length of hospitalization (for those that are followed up till discharge); as well as weight-for-height, weight-for-age and height-for-age z-scores during follow up. The change in these anthropometric indices (z-scores) from admission to discharge will be determined, while controlling for the number of days of hospitalization. Another secondary outcome will be the distribution/antimicrobial sensitivity of pathogens.

Mortality (and other time-to-event data) will be compared between randomized groups using Kaplan Meier curves and Cox proportional hazards regression. WHO reference ranges will be employed to determine the anthropometric z-scores which will be analyzed using linear regression. Other categorical factors will be compared between randomized groups using chi-squared and exact tests, and continuous data using rank-sum tests. The statistical analyses will be performed in STATA version 15 (Stata Corporation, Houston, Texas).

Qualitative data from the in-depth interviews of the mothers will be analyzed using a content thematic approach, using *NVivo software*. We will enroll mothers and perform ongoing analysis until there is saturation of data.

For primary analysis in the PK sub study, sparse PK samples will be obtained from approximately 76 CLHIV. Using NONMEM version 7.3, PK-PD modeling and simulations will be performed to determine primary PK parameters, measures of plasma drug exposure and the dosing requirements.

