This study aims to investigate whether empirical use of an antibiotic with greater antimicrobial sensitivity (ceftriaxone) than standard of care (ampicillin plus gentamicin) will reduce mortality among CLHIV and CHEU admitted with severe acute malnutrition at Mwanamugimu Nutrition Unit, Mulago Hospital. Secondary objectives include: to compare the length of hospitalization, weight-for-height, weight-for-age and height-for-age z-scores between ceftriaxone vs. standard of care (ampicillin and gentamicin) treatment arms. These anthropometric indices and length of hospitalization are hypothesized to be affected by infection related morbidity which may be influenced by the antibiotics received. Other secondary objectives include: to ascertain the frequency of different bloodstream bacterial pathogens and their antimicrobial sensitivities; to ascertain the prevalence of, and factors associated with, HIV-infection among children admitted with severe acute malnutrition at Mwanamugimu Nutrition Unit; and to evaluate the pharmacokinetic (PK) parameters of LPV/r among severely malnourished CLHIV.

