### Study Population

Three hundred children aged 1 month to 5 years (76 CLHIV and 224 CHEU) whose caretakers provide informed consent will be randomized to receive ceftriaxone (*n* = 150) or ampicillin plus gentamicin (*n* = 150). The 1 month to 5-year age group has been selected because it is the most affected by severe acute malnutrition and constitutes over 95% of admissions at Mwanamugimu Nutrition Unit. Also, the 1:3 ratio of CLHIV to CHEU in this sample is reflective of the current proportions of CLHIV and CHEU admitted at Mwanamugimu Nutrition Unit.

Three hundred randomized children provide >80% power to detect reductions in mortality from 28% (average across CLHIV and CHEU in preliminary audits at the unit) to 14% (50% relative reduction; absolute 14% improvement), allowing for 10% non-compliance/loss-to-follow-up (leaving hospital without official discharge) in each group. When half the participants have been enrolled (*n* = 150), the data safety monitoring board (DSMB) will review the preliminary data to determine if these estimates are appropriate. In addition, at least 280 severely malnourished children and their mothers will be tested for HIV at admission; any positive children will also be eligible to participate in the clinical trial. Two hundred eighty children provide 80% power to determine the prevalence of HIV-infection, using the prevalence of HIV-infection of 24% obtained in the probisam study in Mwanamugimu in 2013 (10), as a reference. The CLHIV in the clinical trial on LPV/r will take part in the pharmacokinetic sub-study providing 3 sparse PK samples each.

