### Study Procedures

All severely malnourished children and their mothers will have rapid HIV antibody tests on admission as per routine practice; at least 280 children will participate in the cross-sectional study. Children under 18 months of age with positive HIV results will have blood taken for DNA PCR. The children who test positive or whose mother's test positive (i.e., are CHEU) will be eligible for enrolment into the trial. Participant enrolment will be done between 9.00 am and 4.00 pm from Monday to Friday to allow for blood samples to be taken to the laboratories on the day of enrolment. HIV rapid testing will be done at the unit (Mwanamugimu); HIV DNA PCR at the Baylor Uganda center of excellence (COE) laboratory at the Mulago Hospital Complex. At enrolment, anthropometry and a physical examination will be done; resuscitation will be provided as needed and a blood sample will be taken off for blood culture. The blood culture and sensitivity will be done in the Microbiology laboratory at the Makerere University College of health Sciences (MakCHS). After all enrolment procedures have been done, children will be randomized to ceftriaxone vs. ampicillin/gentamicin. The children will then receive antibiotics as randomized for 1 week together with other routine care. At day 8 (on completion of study medication), the children will be evaluated to ascertain any events that may have occurred and document administration of the study medication. They will then be followed up until discharge/death whichever occurs first. ART naïve CLHIV will initiate ART during admission while ART-experienced children will continue their regimens; both groups will receive daily cotrimoxazole throughout follow-up. The eligible CLHIV on LPV/r (target number – 76) will have 3 sparse PK samples taken at least 2 weeks after ART initiation and at least 1 week after admission to hospital (after they have completed the stabilization phase of treatment); the samples will be taken over 2–3 days depending on what is physiologically possible for the children. The samples will be collected from the study population to cover three time points. The child will take an observed morning dose and then sampling will be done at 3 h, at 6 h and at 12 h (just before the evening dose). LPV concentrations in the plasma samples will be determined using ultra performance liquid chromatography with ultraviolet detection in the Department of Pharmacology and Therapeutics, MakCHS. All laboratories are on the same location on Mulago hill, within a 1 km radius. During admission, the mothers will be interviewed to ascertain sociocultural/ system factors related to antenatal care attendance, prior HIV testing, knowledge and access to PMTCT services, infant feeding practice and ART adherence (theirs and the children's as applicable). Some of the mothers (~20) will be asked to participate in in-depth interviews. These will be consecutively enrolled until data saturation. These interviews will be tape recorded, transcribed verbatim and then translated into English where applicable. Any adverse events that develop will be managed according to the treatment protocols of Mwanamugimu Nutrition Unit/ Mulago Hospital. The principal investigator will be notified of these events within 24 h, who will in turn inform the trial sponsor within 24 h; and the Research Ethical Committee (School of Medicine Research Ethical Committee at Makerere University) within 7 days; and Uganda National Drug Authority within 7 days, as per the local research guidelines.

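### Length of hospitalization is compared only in children followed to discharge, so the comparison conditions on survival and is not protected by randomisation

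*Protocol article*

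**What the plan says.** Under Data Management and Statistical Analysis, the outcome is "length of hospitalization (for those that are followed up till discharge"). Study Procedures states "They will then be followed up until discharge/death whichever occurs first", and the trial schema (Table 1) has separate rows for death and discharge. A child who dies is therefore not followed to discharge and drops out of this outcome. So does a child who leaves before formal discharge, which Study Population counts as loss to follow-up.

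The same analysis section says "The primary outcome will be in hospital mortality". Study Population plans for that event to differ by arm: "Three hundred randomized children provide >80% power to detect reductions in mortality from 28"% "to 14% (50% relative reduction; absolute 14% improvement), allowing for 10% non-compliance/loss-to-follow-up" in each group.

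Stay is meant as a treatment comparison, not as a description of survivors. The Introduction lists it among the outcomes compared between arms and says the anthropometric indices and "length of hospitalization are hypothesized to be affected by infection related morbidity which may be influenced by the antibiotics received".

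On method, the analysis section states "Mortality (and other time-to-event data) will be compared between randomized groups using Kaplan Meier curves and Cox proportional hazards regression", and gives rank-sum tests for continuous data. It does not say which of these applies to stay. For this outcome the Discussion names only social factors as a limitation.

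**The concern.** Randomisation makes the arms comparable at entry. It does not make the children discharged from each arm comparable when treatment affects who is discharged. Here the filter is the primary outcome itself. If ceftriaxone works as planned, its discharged group contains children who would have died on ampicillin plus gentamicin, and nobody in the control discharged group corresponds to them. A difference in stay then mixes any effect of the antibiotic on duration with a difference in who is being measured.

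The second exclusion, of children who leave early, adds a further selection if leaving is related to prognosis or to arm in this open-label trial.

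At stake is how a secondary result is read. An apparent lengthening of stay could be held against a drug that saves lives, or a real shortening could go unseen.

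**Working it through.** **Inputs from the article.** 150 children per arm; mortality 28% on control and 14% on ceftriaxone; 10% allowance for non-compliance or loss in each group.

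**Assumptions, not in the article.** Two-sided alpha of 0.05. No child who would survive on control dies on ceftriaxone. Loss unrelated to survival. Rescued children (those who survive only because of ceftriaxone) stay D days longer than other survivors, with D varied. No true effect of the drug on stay unless stated.

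**Step 1: reproduce the plan's figure.** Without continuity correction:

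n per arm = [1.960 x sqrt(2 x 0.21 x 0.79) + 0.842 x sqrt(0.28 x 0.72 + 0.14 x 0.86)]^2 / 0.14^2 = 132 (rounded up).

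132/0.9 = 147 per arm (rounded up), 294 in total, against 300 planned. Power is 81.0% with 135 per arm and 84.9% with 150. The stated size is reproduced, so 28% and 14% are the rates to carry forward.

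**Step 2: who enters the comparison.**
- Control: 150 x 0.72 = 108. Ceftriaxone: 150 x 0.86 = 129. The difference is 21.
- If the whole 10% allowance is loss: 135 x 0.72 = 97.2 and 135 x 0.86 = 116.1.
- Share of discharged ceftriaxone children who would have died on control: 21/129 = 0.14/0.86 = 16.3%. Loss unrelated to survival leaves this share unchanged.

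At most 72% of children can survive on both arms, so the share is at least (0.86 - 0.72)/0.86 = 16.3%. The no-harm assumption makes it exactly that.

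**Step 3: shift in the mean.** Let m be the mean stay of children who survive on either arm.

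Ceftriaxone mean = [0.72m + 0.14(m + D)]/0.86 = m + 0.163D. Control mean = m.

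**Step 4: effect on the test.** A simulation used 4,000 trials per scenario, 150 per arm, 10% random loss, and lognormal stay with an assumed median of 14 days and log-SD of 0.5. It counted two-sided rank-sum p < 0.05 in the direction of longer stay on ceftriaxone (nominal 2.5%).

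| D (days) | Shift in mean (days) | False finding of longer stay |
|---|---|---|
| 0 | 0.0 | 2.6% |
| 3 | +0.5 | 7.4% |
| 5 | +0.8 | 13.0% |
| 7 | +1.1 | 19.6% |
| 10 | +1.6 | 27.2% |
| 14 | +2.3 | 37.3% |

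If rescued children stayed 3 days less than other survivors, the shift would be -0.5 day, so the sign follows D.

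**Step 5: masking.** With a true shortening of 1 day and D = 7, the expected difference is 0.163 x 7 - 1 = +0.1 day. In the simulation, significant shortening was found in 18.0% of trials at D = 0 and in 2.4% at D = 7.

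**The case against.** A reader might infer that an effective drug will appear to prolong stay. The article does not support that. The direction requires rescued children to stay longer than other survivors. This is plausible, but the article gives no data on stay, by severity or otherwise. It also raises the possibility that the antibiotics influence stay through morbidity, and a real shortening would push the other way. Even at D = 14 a significant false lengthening is the less likely result (37.3%), and at D = 0 the error rate is nominal. This limits the claim about direction. It does not restore comparability between the discharged groups.

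Other points, and what stands of each:

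- **The restriction may be aimed mainly at early leavers.** Possibly, but as worded it also removes deaths, since follow-up ends at discharge or death as separate events.
- **The analysis plan may settle it, or Kaplan-Meier and Cox may cover it.** The restriction is written into the outcome definition, so it is a stated choice rather than a detail left open. Either time-to-event methods or a rank-sum test applied within the restricted set still condition on survival.
- **Duration among survivors is a legitimate question.** As description, yes. As a contrast between randomised arms it needs assumptions the article does not state.
- **It is only a secondary outcome, and mortality will be reported beside it.** True, and this bounds the importance of the point.

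**Conclusion.** The point holds in this form: the planned comparison of stay conditions on a post-randomisation event that is the primary outcome, and nothing else in the article corrects for it. At the planned rates 16.3% of the discharged ceftriaxone group has no control counterpart, if no child is harmed by the switch and loss is unrelated to survival. That figure comes from the protocol's own rates.

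The size of the distortion, 0.163 x D days, does not, because D is unknown. Over the assumed range of 0 to 14 days it runs from nothing to +2.3 days. The supported statement is that the result can be biased toward longer stay or can conceal a shortening, not that it will be. The test error rates depend further on the assumed distribution of stay. The primary mortality analysis and the sample size stand. The change should be made, as a matter of modest weight.

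**What to change.** Redefine the between-arm outcome as time to live discharge in all randomised children, with death as a competing event. Report the cumulative incidence of live discharge by arm, with a Fine-Gray model for the comparison.

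An alternative is a rank-sum test on stay with deaths given the worst rank. This is a different analysis, not an equivalent one: it weights differences differently, and an ordinary rank-sum test cannot take censored stays, so it needs its own stated rule for children who leave early.

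In the time-to-event analysis, censor children who leave before formal discharge on the day they leave. That assumes leaving is unrelated to prognosis, so add a sensitivity analysis, for example counting them first as discharged that day and then as never discharged alive. Keep stay among discharged children as a descriptive summary by arm, shown beside mortality.

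**Cost.** Mainly analysis wording, fixed before results by arm are known. Death and discharge are already recorded in the trial schema. The sponsor should confirm that the date of an informal departure is captured, since Table 1 has no separate row for it.

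**Downside.** The new outcome partly reflects mortality, overlaps with the primary result, and no longer measures duration of stay alone. The report should say so.

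### The z-score outcomes need a discharge measurement, so the planned regression compares survivor subsets whose make-up differs by arm if mortality falls as designed

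*Protocol article*

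**What the plan says.** The protocol article, under Data Management and Statistical Analysis, first lists the three z-scores as follow-up outcomes without a time point. It then fixes the contrast: "The change in these anthropometric indices (z-scores) from admission to discharge will be determined", controlling for days in hospital. The method follows in the next paragraph: "WHO reference ranges will be employed to determine the anthropometric z-scores which will be analyzed using linear regression".

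Study Procedures sets the end of observation: "They will then be followed up until discharge/death whichever occurs first". The sample size text in Study Population names a second route out of the trial, "allowing for 10% non-compliance/loss-to-follow-up (leaving hospital without official discharge) in each group". The design effect is in the same place: "Three hundred randomized children provide >80% power to detect reductions in mortality from 28"% "to 14% (50% relative reduction; absolute 14% improvement").

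For length of hospitalisation the article restricts the outcome to children whose follow-up reaches discharge. For the z-scores it states no population. Study Procedures names anthropometry only at enrolment. Table 1 marks a clinical assessment on day 8 and at discharge or death, without saying whether weight and height are taken.

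**The concern.** The outcome as defined does not exist for a child who dies. This goes beyond ordinary missing data: imputation cannot sensibly supply a discharge z-score for a child who was never discharged. Death is also the primary outcome, and the trial is designed to halve it.

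If ceftriaxone works as hoped, its discharged group will include children who would have died on standard of care, while their counterparts in the control arm drop out of the comparison. The regression then no longer compares the randomised groups. The introduction presents the z-scores as comparisons between treatment arms, so a reader would take the coefficient as a treatment effect on growth. It could understate or overstate any nutritional benefit, and it could appear to conflict with the mortality result with no biological reason.

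**Working it through.** **Inputs.** From Study Population: 150 children per arm, mortality 28% (control) and 14% (ceftriaxone), and a 10% allowance per arm for non-compliance and loss combined. Two-sided alpha of 0.05 is assumed, because the article does not state it.

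**Reproducing the stated figure.** The usual two-proportion formula without continuity correction, at 80% power, gives 132 per arm. Then 132/0.90 = 147 per arm, or 294 in total against the planned 300. Power is 81.0% at 135 per arm (150 × 0.90) and 84.9% at 150. The claim of more than 80% holds, so these figures can be taken as the design assumptions.

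**Children without a discharge z-score.**

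| Assumption | Control | Ceftriaxone | Overall | Scored | Gap (points) |
|---|---|---|---|---|---|
| Deaths only | 28% | 14% | 21% | 108 vs 129 | 14 |
| Deaths, then 10% of survivors leave: 1 - (1 - m) × 0.90 | 35.2% | 22.6% | 28.9% | 97 vs 116 | 12.6 |
| Deaths plus the full 10%: m + 0.10 | 38% | 24% | 31% | 93 vs 114 | 14 |

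**Precision.** In SD units of the z-score change, SE = sqrt(1/93 + 1/114) = 0.140. With 97 and 116 scored it is 0.137.

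**Bound on survivor bias.** Suppose ceftriaxone causes no deaths. The share of ceftriaxone survivors who would have died on control is (0.28 - 0.14)/0.86 = 16.3%. Trimming that share from either tail of a normal distribution of change (cut at 0.98 SD) shifts the mean by φ(0.98)/0.837 = 0.29 SD. The bound is therefore ±0.29 SD, about 2.1 SE.

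**Bias for a given gap in gain.** The shift is 0.163 × gap. If the children saved gain 0.25, 0.5 or 1.0 SD less than other survivors (assumed values), the contrast moves against ceftriaxone by 0.04, 0.08 or 0.16 SD. If they gain the same, it does not move. If they gain more, it moves in favour of ceftriaxone.

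**Threshold model.** Let a normal severity score cause death above a cut-off, and let it correlate ρ with poor gain (ρ is assumed). The mean gain among survivors is raised by ρ × φ(c)/(1 - m), where c is the cut-off:
- Control, m = 0.28: 0.337/0.72 = 0.468ρ.
- Ceftriaxone, m = 0.14: 0.223/0.86 = 0.259ρ.
- Bias = (0.259 - 0.468)ρ = -0.209ρ, which is -0.06 SD at ρ = 0.3 and -0.10 SD at ρ = 0.5 (0.45 to 0.75 SE).

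If mortality falls only to 21%, the ceftriaxone term is 0.288/0.79 = 0.365ρ. The bias is then -0.103ρ, or -0.03 to -0.05 SD. With equal mortality it is zero.

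None of these calculations includes the planned adjustment for days in hospital, so they show the selection effect alone.

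**The case against.** The strongest reply is that handling of deaths and missing secondary data is commonly left to the analysis plan, which is not shown. That stands for any complaint that a missing-data method is absent. It does not remove the point, because the admission-to-discharge contrast and the linear regression are both written in the article, and together they leave a death with no value.

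A second reply is that the wording about z-scores during follow-up, with the day 8 assessment, leaves room for interim values. This stands in part. However, the sentence that follows fixes the contrast at discharge, and day 8 weight and height are not documented.

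A reader might also infer that 31% of children will be unscored. The documents do not support that as a single figure: the 10% mixes non-compliance with loss, and a non-compliant child who is discharged can still be measured. Hence the range from 21%.

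A reader might further infer that the comparison is biased against ceftriaxone. Nothing in the article says that children saved by the drug gain less than other survivors. That is plausible, but it is an assumption, and the bound runs in both directions. The figures also lean on the full 50% reduction, which the Discussion itself calls unusual.

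Finally, a worst-rank test as the main analysis would largely repeat the mortality comparison, since about 21% of children would sit at the bottom because they died. That objection stands, so such a test belongs in a sensitivity analysis.

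**Conclusion.** The concern holds in limited form. Followed as written, the z-score regression compares children selected by surviving to official discharge. Under the design assumptions about 21% to 31% of children are unscored, with 12.6 to 14 points more in the control arm.

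The resulting bias is possible, not established. It is at most ±0.29 SD at the design effect, given no deaths caused by ceftriaxone and a normal distribution of change. It is -0.06 to -0.10 SD if severity correlates 0.3 to 0.5 with poor gain, about half that for a fall to 21%, and absent in expectation if mortality does not differ. The modelled values are below one standard error. The problem therefore matters most if the trial succeeds on its primary outcome. That outcome, in-hospital mortality, is not affected.

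**What to change.** In Data Management and Statistical Analysis:

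1. State that the z-score regression is conditional on being discharged alive and is not to be read as a randomised treatment effect on growth.
2. Report it beside the mortality result, with trimming (survivor) bounds for unequal survival.
3. Pre-specify a sensitivity analysis in which deaths take the worst rank, compared between arms by the rank-sum test that the section already lists.
4. For children who leave without official discharge, use multiple imputation from admission values. Add day 8 values only if weight and height are recorded then, and say whether they are.

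This should be settled before any data are compared by arm, because the trial is open label and a later choice could look driven by results.

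The cost is a few sentences and a little more analysis, with no new visits. The ranked result mixes death with growth and is hard to express in z-score units, so it must be read with the mortality result.

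### The z-score change analysis adjusts for days in hospital, a post-randomisation secondary outcome; if arm affects stay, the adjusted coefficient is not the effect of randomised treatment

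*Protocol article*

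**What the plan says.** All references are to the protocol article.

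- **Covariate.** In Data Management and Statistical Analysis, the change in the three z-scores between admission and discharge "will be determined, while controlling for the number of days of hospitalization".
- **Model.** The next paragraph of that section refers to "anthropometric z-scores which will be analyzed using linear regression".
- **The covariate is also an outcome.** The same section states: "Secondary outcomes will be: length of hospitalization (for those that are followed up till discharge".
- **Both are between-arm objectives.** The Introduction sets out "to compare the length of hospitalization, weight-for-height, weight-for-age and height-for-age z-scores between ceftriaxone vs. standard of care".
- **The hypothesised mechanism.** The Introduction adds: "These anthropometric indices and length of hospitalization are hypothesized to be affected by infection related morbidity which may be influenced by the antibiotics received".
- **Timing.** Study Procedures says of the children, after the day 8 evaluation: "They will then be followed up until discharge/death whichever occurs first". The number of days is therefore fixed only at the end of follow-up, well after randomisation.

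The article does not describe the stay-adjusted result as a mediation or direct-effect estimate, does not call it exploratory, and does not explicitly set a version without the adjustment beside it.

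**The concern.** A covariate in a randomised comparison is safe when treatment cannot have changed it. Length of stay does not meet that condition here. On the article's own account the antibiotic may alter infection morbidity, which may in turn alter both stay and growth. Adjusting for stay then has two consequences.

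1. Any part of the antibiotic's effect on z-scores that runs through stay is taken out of the estimate.
2. Children with the same stay in the two arms are no longer alike. If one antibiotic shortens stay, a child who stays 18 days on that arm tends to be sicker than a child who stays 18 days on the other. If sicker children also grow less, the model reports an arm difference that the drug did not cause through growth.

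Two features of the design make this more than theoretical. The trial is open label, so the timing of discharge can depend on knowledge of the arm. The Discussion also concedes that social factors will be hard to control for these outcomes, and such factors may drive both discharge and growth. At stake is the interpretation of the adjusted change in three anthropometric indices.

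**Working it through.** The plan states no figure that depends on this covariate, so there is nothing of its own to reproduce. The check is what the model estimates when arm shifts stay.

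**Check 1: large-sample simulation (2,000,000 children per scenario; all values assumed).**

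Let A be arm (1 = ceftriaxone), U unmeasured severity (mean 0, SD 1), and k the days by which ceftriaxone shortens stay.

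- Stay: L = 18 - kA + 3U + error (SD 4), so the within-arm variance of L is 9 + 16 = 25.
- z-change: Y = dA + bL - cU + error (SD 0.6), with d the direct effect, b the gain per day and c the effect of severity on growth.
- True total effect of arm: d - bk.
- Coefficient after adjusting for L: d - c(3/25)k.

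| k (days) | d | b | c | True total | Unadjusted | Adjusted for stay |
|---|---|---|---|---|---|---|
| 0 | 0.2 | 0.04 | 0.3 | 0.200 | 0.200 | 0.200 |
| 2 | 0 | 0 | 0.3 | 0.000 | 0.001 | -0.071 |
| 4 | 0 | 0 | 0.3 | 0.000 | -0.000 | -0.144 |
| 4 | 0.2 | 0.04 | 0 | 0.040 | 0.041 | 0.200 |
| 4 | 0.2 | 0.04 | 0.3 | 0.040 | 0.040 | 0.056 |

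Hand check of row 3: 0 - 0.3 × 0.12 × 4 = -0.144. The unadjusted model recovers the total effect throughout. The adjusted model agrees with it when k = 0 and otherwise misses it, by about +0.01 to +0.16 or -0.07 to -0.14 over all the scenarios run.

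**Check 2: type I error at roughly the trial's size.**

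From Study Population: 300 randomised, mortality 28% and 14%, 10% non-compliance or loss. Treating the whole 10% as loss, mean mortality is (28 + 14)/2 = 21%, so deaths are 0.21 × 300 = 63, losses are 30, and 300 - 63 - 30 = 207 are discharged alive.

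Assumed, because the article does not give them: SD of z-change 1, SD of stay 7 days, ceftriaxone shortens stay by k days with no effect on z-score, within-arm correlation r between stay and z-change.

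- Spurious arm coefficient = k × r × 1/7.
- SE before allowing for the arm-stay association = 2√(1 - r²)/√207.
- Variance inflation for that association = 1 + (k²/4)/49, which is 1.020 for k = 2 and 1.046 for k = 3; the SE is multiplied by its square root.
- Type I error = P(|Z + coefficient/SE| > 1.96).

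| k | r | Coefficient | SE | Type I error |
|---|---|---|---|---|
| 1 | -0.25 | -0.036 | 0.135 | 5.8% |
| 1 | -0.50 | -0.071 | 0.121 | 9.1% |
| 2 | -0.10 | -0.029 | 0.140 | 5.5% |
| 2 | -0.25 | -0.071 | 0.136 | 8.2% |
| 2 | -0.50 | -0.143 | 0.122 | 21.7% |
| 3 | -0.25 | -0.107 | 0.138 | 12.2% |
| 3 | -0.50 | -0.214 | 0.123 | 41.3% |

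Without the variance inflation the last row would be 43%; about 41% is the better figure. A positive r reverses the sign of the coefficient.

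**The case against.** **The adjustment has a reasonable purpose.** Discharge z-scores are taken after unequal time in hospital. In the fourth row of the simulation table the unadjusted estimate is 0.04 although the direct effect is 0.20, because a shorter stay leaves less time to gain weight. This stands as a caution: the total effect is the right answer to the randomised question, but at discharge it mixes growth with observation time. It does not justify conditioning on an outcome in the main comparison.

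**The sentence may be descriptive.** It does not itself mention arms, the secondary outcome is worded as z-scores during follow-up, and the sentence on linear regression does not mention days. A separate z-score analysis without the adjustment is therefore possible. Since the Introduction makes the z-scores a between-arm comparison, the covariate reading is the more natural one, but it is not beyond doubt. A reader might infer that all three z-score comparisons have lost the protection of randomisation; the text does not settle that.

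**Bias is conditional.** A reader might infer that the estimate is certainly biased. The documents do not support this: the article says only that the antibiotics may have an influence, and with no effect on stay the two models agree.

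**Baseline.** A reader might also infer that the plan leaves out the admission z-score. The article is condensed and lists no full covariate set, so its silence shows nothing.

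**Conclusion.** The point holds in conditional form. The article specifies an adjustment for a post-randomisation variable that is itself a secondary outcome and that, by its own hypothesis, may respond to treatment. If arm affects stay, the adjusted coefficient does not estimate the effect of randomised arm on z-score change.

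Neither size nor direction can be derived from the document. The illustrative range of -0.07 to -0.21 z, with type I error of about 8% to 41%, rests on assumed stay shifts of 2 to 3 days, correlations of -0.25 to -0.50 and the assumed SDs. The upper end is a corner of those assumptions and should not be read as a forecast; a small shift or a weak correlation leaves the error close to 5%.

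Severity: should be fixed. Only secondary outcomes are involved, and the primary analysis of in-hospital mortality is unaffected.

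**What to change.** 1. Remove days of hospitalization from the main between-arm z-score model. Regress the discharge z-score (or its change) on arm and admission z-score.
2. If a stay-adjusted model is kept, label it exploratory and state that its arm coefficient has no causal reading.
3. If unequal time to discharge is a concern, add a fixed-time z-score as an optional supportive analysis. Table 1 schedules a clinical assessment on day 8, but neither it nor Study Procedures says that weight and length are recorded then, so this depends on whether they are.
4. State the limits that remain: the discharge comparison reflects unequal observation time and covers only children who reach discharge. Dropping the covariate cures neither.

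Steps 1, 2 and 4 cost only a change of wording before analysis. Step 3 may need extra measurements and adds an analysis at a different time point, so it should support the discharge comparison and not replace it.
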